## 8.2 STUDY SITE

90 villages in the catchment areas of Zomba Central hospital in southern Malawi. This hospital participated in previous related studies [1, 2, 6] and is particularly suitable for the delivery trial because of the existing linkages with community based health care providers and rural clinics within their catchment areas. In addition, it is close to the College of Medicine where procurement of study resources will be done.

## 8.3 SAMPLE SIZE

Although a factorial design will be used, only the main effects of PMC mode of delivery and the “use of SMS/HSA reminders” are of primary interest. There are five arms in total as described above such that each of the four intervention arms will be compared to the control arm (Arm 1: Mother given at discharge without SMS reminder). Each village cluster contributes 2 to 4 children/year on average with severe anaemia. Thus, the cluster sizes vary and we have accounted for this in sample size calculations in order to achieve the number of clusters that would have enough power to detect the desired difference. The sample size calculation has been adjusted in the design effect using the coefficient of variation method [11-13]. This has assumed that the cluster sizes will be uniformly distributed between 2 and 4 children i.e. U[2,4]. This gives a mean cluster size of 3 children per village per year and a standard deviation of cluster sizes of 0.58. Hence the coefficient of variation of cluster sizes (CV) is  $0.58/3 = 0.19$  and  $CV^2 = 0.036$ . Assuming an

intra-cluster correlation coefficient (ICC) of 0.1 and allowing for 10% loss-to-follow-up, a sample size of 25 clusters of an average of 3 children per village (75 children per arm, N=375 overall (for 125 clusters for the 5 arms)) has 80% power to detect a 25% absolute increase in uptake from an estimated 50% in the OPD and delivery at home groups to 75% in the arms supported by SMS reminders ( $\alpha=0.05$ ). The ICC of 0.1 is slightly more conservative than the ICC in a previous trial of delivery approaches for IPTc in the Gambia (0.08)[14].

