### 8.10 EXPECTED DURATION OF TRIAL

The total duration of the trial for a participating mother/guardian-child pair is 3.5 months. Participant recruitment will occur for 30 months. There will be 4 months of follow-up of the last recruited subject and finally 6 months to complete data analysis and study reporting. The end of trial will be defined as the final assessment of the last participant within the trial, unless additional time is needed for follow-up of a trial-associated adverse event. This new protocol is a continuation of COMREC study P.02/15/1679.

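### Section 8.3 uses the range of average village yields (2 to 4 a year) as the distribution of actual cluster sizes, which omits chance variation in small counts and overstates power by about 3 points if counts are Poisson

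*Protocol*

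**What the plan says.** Protocol section 8.3 starts from the yield of a village: "Each village cluster contributes 2 to 4 children/year on average with severe anaemia". It then turns this into a distribution of cluster sizes: "This has assumed that the cluster sizes will be uniformly distributed between 2 and 4 children i.e. U[2,4"]. The summary figures follow: "This gives a mean cluster size of 3 children per village per year and a standard deviation of cluster sizes of 0.58", hence a CV of 0.19 and a squared CV of 0.036. These enter the design effect: "The sample size calculation has been adjusted in the design effect using the coefficient of variation method [11-13"].

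The result is stated under these conditions: "intra-cluster correlation coefficient (ICC) of 0.1 and allowing for 10% loss-to-follow-up, a sample size of 25 clusters of an average of 3 children per village". That is 75 children per arm and 375 in 125 clusters. According to the section, this design "has 80% power to detect a 25% absolute increase in uptake from an estimated 50% in the OPD and delivery at home groups". The target rate is 75%, for arms that get SMS reminders, at alpha 0.05.

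Three other places bear on cluster size. Section 8.10 states: "Participant recruitment will occur for 30 months". Sections 8.2 and 8.7.4.2 give 90 villages. Section 11.7.1 gives 102 clusters, repeats the 2 to 4 a year without calling it an average, and covers varying cluster size only through a combined 20% allowance.

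**The concern.** The CV method needs the spread of the sizes that clusters actually reach. Here a cluster's size is the number of its children who are admitted with severe anaemia and enrolled. Even if every village had the same underlying rate of 3 a year, some would contribute one child and others five. Section 8.3 carries only the spread between village averages and leaves out the scatter of counts around each average. At means this small, the scatter is the larger part under any Poisson-like model.

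The assumed distribution allows no village with 0, 1 or 5 or more children. The protocol describes no quota, minimum or cap per village that would hold counts inside 2 to 4. The SD of 0.58 is also that of a continuous uniform variable, which suits rates better than whole children.

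Section 8.3 says that varying cluster size has been accounted for, so a reader takes the stated 80% as already net of it. The stated size has almost no slack above 80%, and this omission can only push true power below the stated figure.

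**Working it through.** **Inputs from section 8.3:** uptake 50% v 75%, alpha 0.05 (two-sided assumed, as sidedness is not stated), ICC 0.1, 10% loss, 25 clusters averaging 3 children per arm, squared CV 0.036.

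**Formulas**
- Design effect DE = 1 + [(1 + CV²)m − 1] × ICC, where m is the mean cluster size.
- Unpooled size per arm before clustering: (1.960 + 0.842)² × (0.5×0.5 + 0.75×0.25) / 0.25² = 7.849 × 0.4375 / 0.0625 = 54.9.
- Effective size per arm: 75 × 0.9 / DE = 67.5 / DE.
- Power = Φ(0.25 / √(0.4375 / effective size) − 1.960).

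**1. Reproduce the protocol's figure**
- SD of U[2,4] = 2/√12 = 0.577; CV = 0.577/3 = 0.19.
- DE = 1 + (1.036 × 3 − 1) × 0.1 = 1.211.
- Children needed: 54.9 × 1.211 / 0.9 = 73.9 per arm, or 24.6 clusters, rounded to 25 clusters and 75 children.
- Effective size 67.5 / 1.211 = 55.7; power 80.6%. The pooled-variance formula gives 78.6%.

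The stated size and 80% power therefore follow from the stated inputs.

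**2. Use whole children, with no Poisson assumption.** If sizes 2, 3 and 4 are equally likely, SD = √(2/3) = 0.82 and CV = 0.27. Then DE = 1.222 and power is 80.2%. The loss is only 0.4 points, but 0.19 is not the CV even of whole-number sizes spread evenly over 2, 3 and 4.

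**3. Add chance variation in the counts.** The documents give no count distribution, so Poisson is an assumption. If a village's count is Poisson around its own rate, and rates are uniform with the relative spread of U[2,4], then CV² = 1/m + (0.577/3)² = 1/m + 0.037.

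| Mean children per village | CV² | CV | 0.19 as a share of it |
|---|---|---|---|
| 3 (section 8.3) | 0.333 + 0.037 = 0.370 | 0.61 | 0.31 |
| 4.2 (75 children over 90/5 = 18 villages per arm) | 0.240 + 0.037 = 0.277 | 0.53 | 0.36 |
| 7.5 (30 months at 3 a year) | 0.133 + 0.037 = 0.170 | 0.41 | 0.46 |

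At a mean of 3, about 59% of villages would have 2 to 4 children and about 6% none.

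**4. Effect on section 8.3's own design (25 clusters of 3 per arm)**
- DE = 1 + (1.370 × 3 − 1) × 0.1 = 1.311.
- Effective size 67.5 / 1.311 = 51.5; power 77.4% (75.3% pooled).
- Loss: 80.6 − 77.4 = 3.2 points.
- Restoring 80% would take 54.9 × 1.311 / 0.9 = 80 children, or 27 clusters, per arm.

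**5. Sensitivity at mean 3**
- A zero-truncated Poisson (only villages with at least one child count) gives CV 0.52 and power 78.3%.
- Over ICC 0.05 to 0.2 the loss runs from 1.6 points (84.0% to 82.3%) to about 5.7 points (74.0% to 68.4%).

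**6. Keep the number of villages apart.** With 18 villages per arm and 75 children:
- on section 8.3's squared CV of 0.036, DE = 1.332 and power is 76.8%;
- with count variation, DE = 1.432 and power is 73.7%.

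Of the fall from 80.6% to 73.7%, 3.8 points come from fewer, larger clusters and 3.1 from the CV.

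**The case against.** The best defence is that section 8.3 makes no calculation error and openly labels the uniform distribution an assumption. That stands: the fault is the choice of input.

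Section 11.7.1 gives 2 to 4 a year without calling it an average, so one could read the range as actual yearly yields. This weakens the point but does not remove it. Section 8.3 is the passage that derives the CV and it does say average, and nothing in the protocol would confine villages to that range.

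The loss is also modest beside other choices. Pooled or unpooled variance alone moves power by 2 points. Section 8.3 takes ICC 0.1 where the earlier trial it cites had 0.08; at 0.08, power with CV 0.61 is 79.4%. The design-effect formula weights every child equally. If the cluster-adjusted regression in section 11.7.4 weights clusters efficiently, which it does not specify, power with count variation is 78.2% at ICC 0.1 and 79.9% at 0.08. All of this stands and limits the severity.

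A reader might go further in three ways that the documents do not support:
- *That 0.19 is a third of the real CV.* No real CV is given. A third holds only for Poisson counts at about 3 to 4 children per village; at 7.5 it is nearer a half, and a cap on enrolment per village would reduce the variation.
- *That many villages will be empty.* The 6% belongs to a one-year mean of 3. Under the same model it is 2.1% at 4.2 per village and 0.13% at 7.5.
- *That this omission brings power to the low 70s.* That figure also contains the conflict over the number of villages, a separate matter.

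**Conclusion.** The point holds as a fault in the distributional input. Section 8.3 uses the spread of village averages where its method needs the spread of realised counts, so the CV is too low and the stated power too high. Under Poisson counts the stated CV is about a third to a half of what it should be, depending on how many children a village finally contributes. On the section's own design this costs about 3 points, from 80.6% to about 77%. These figures rest on the Poisson assumption, the unpooled formula, ICC 0.1, 10% loss and a two-sided test.

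Severity is minor to moderate. No design decision turns on 3 points, but the section claims to have dealt with this variation and leaves no margin for it. The mean cluster size matters as much or more: at 8.3's own CV with 75 children per arm, power is 76.8% at 4.2 children per village and 66.9% at 7.5.

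**What to change.** Keep the sample size. In section 8.3, replace CV 0.19 with the CV of realised counts per village. Section 4.1 lists the trial as recruiting, so this can be estimated from enrolment per village to date. Failing that, use CV² = 1/mean + 0.037 and state the Poisson assumption. Then restate the design effect and power: about 1.31 and 77% with 25 clusters of 3 per arm.

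Separately, settle how many villages take part (90, 102 or 125) and what cluster size is expected over 30 months, and enter that mean in the same formula. With 90 villages and 375 children, power is 76.8% on the section's own CV and about 74% with count variation added.

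The cost is one recalculation and a revised sentence or two, with no change to conduct. The stated power would fall by about 3 points on this account.

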**Study Interventions:** All children will receive Dihydroartemisinin-piperaquine (3-day treatment courses, given 2, 6 and 10 weeks after discharge) either: a) at discharge + SMS Reminder; b) at discharge + No SMS Reminder; c) at discharge + HSA Reminder; d) at OPD + SMS Reminder; or e) at OPD + No SMS Reminder

**Outcome Measures:** Primary: 100% of PMC drugs uptake (defined as administration of **all** 3-day treatment courses, given 2, 6 and 10 weeks after discharge) assessed by unannounced spot checks.

**Follow-up procedures:** Children will be followed up for 15 weeks by passive case detection in 2 phases: Pre-PMC (2 weeks between hospital admission and 2 weeks post-discharge); PMC (2-14 weeks post-discharge)

**Sample Size:** A sample size of 75 children per arm (375 total children) allows for a detection of 25% increase in uptake from 50% to 75% with 10% loss to follow-up (power 90%,  $\alpha=0.05$ ).

**Data Analysis:** The % of children receiving IPTpd according to schedule will be compared by relative risks (95% CI), adjusted for prognostic factors at baseline using log binomial or Poisson regression with adjustment for cluster effects

**Partner Institutions:** University of Bergen; Makerere University; KEMRI-CDC, Kenya; University of Minnesota; Liverpool School of Tropical Medicine; London School of Hygiene & Tropical Medicine; Imperial College London; University of Amsterdam; US Centers for Disease Control and Prevention, University of North Carolina, and University of Massachusetts.

Table1 : Study treatment and phases

| [figure not shown] |                                                     |                                                                                                                                                                                                                              |
|-------------------------------------------------------------------------------------|-----------------------------------------------------|------------------------------------------------------------------------------------------------------------------------------------------------------------------------------------------------------------------------------|

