#### **11.7 STATISTICS AND DATA ANALYSES**

##### **11.7.1 Sample Size and randomization**

Although a 2x2 factorial design will be used, only the main effects of "place of delivery" and "use of mobile phone reminders" are of primary interest. Each village cluster contributes 2 to 4 children/y with severe anaemia and there are 102 clusters in the catchment area. Assuming an intra-cluster correlation coefficient (ICC) of 0.1 and allowing for 20% loss-to-follow-up or efficiency loss due to varying cluster sizes, a sample size of 19 clusters of 5 children per arm (95 per arm, N=380 overall) has 80% power to detect a 25% absolute increase in coverage from an estimated 50% in the standard VHV or OPD groups to 75% in the arms supported by mobile phone reminders ( $\alpha=0.05$ ). The ICC of 0.1 is slightly more conservative than the ICC in a previous trial of delivery approaches for IPTc in the Gambia (0.08)[14].

The trial will use villages as the unit of randomisation; i.e. it is a cluster-randomised trial. This trial uses a factorial design and will evaluate two interventions, and will have 4 arms (factorial design). These kind of trials need to take the clustering in variation at village level into account, also called the design effect.

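### Section 8.3 draws its 80% pairwise power from 125 villages, but the trial is described as having 90; the summary claims 90% power for the same 75 children per arm.

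*Protocol*

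**What the plan says.** Section 8.3 sets out a five-arm trial in which each of four arms is compared with Arm 1. It assumes a mean of 3 children per village, a squared coefficient of variation of 0.036, an ICC of 0.1 and 10% loss. It arrives at "a sample size of 25 clusters of an average of 3 children per village (75 children per arm, N=375 overall (for 125 clusters" over five arms) and states that this "has 80% power to detect a 25% absolute increase in uptake", from 50% to 75%, at alpha 0.05.

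Three other places in the protocol bear on this calculation.

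- **Village count.** Section 8.2 gives the site as "90 villages in the catchment areas of Zomba Central hospital in southern Malawi". The narrative summary (4.2) and the randomisation section (8.7.4.2) give the same 90, the latter with 1:1 allocation.
- **Power.** For the same 75 per arm and 375 in total, section 4.2 states "detection of 25% increase in uptake from 50% to 75% with 10% loss to follow-up (power 90" per cent).
- **A different design.** Section 11.7.1 describes a 2x2 factorial trial with four arms and 20% loss, in which "a sample size of 19 clusters of 5 children per arm (95 per arm, N=380 overall) has 80% power".

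**The concern.** In a cluster-randomised trial the number of clusters drives power as much as the number of children. The calculation in 8.3 needs 35 more villages than the trial is said to have (125 − 90 = 35). Spreading the same 375 children over 90 villages makes the clusters larger and raises the design effect. Keeping 3 children per village instead loses 105 children (375 − 270 = 105). Either way, the stated 80% does not follow from the design described.

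Separately, one design cannot have both 80% and 90% power for one contrast. A reader or an oversight committee cannot tell from the protocol which village count, arm count, total size or power applies. The point matters most when a single reminder or delivery arm is compared with Arm 1 and the difference is not significant.

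**Working it through.** **Inputs.** From section 8.3: uptake 0.50 versus 0.75, alpha 0.05, ICC 0.1, loss 10%, mean cluster size m = 3, CV² = 0.036. From 8.2 and 8.7.4.2: 90 villages, 1:1 over five arms, so 90/5 = 18 per arm. The protocol does not state sidedness; two-sided is assumed. It does not say which variance formula was used, so ranges run from pooled (lower) to unpooled (higher).

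**Formulas.**
- Unpooled size per arm without clustering: n₀ = (1.960 + z_power)² × (0.25 + 0.1875) / 0.25²
- Design effect: DE = 1 + ((1 + CV²) × m − 1) × ICC
- Effective size per arm: n_eff = villages × m × 0.9 / DE
- Unpooled power: Φ(0.25 / √(0.4375 / n_eff) − 1.960)

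**1. Reproducing 8.3.** n₀ = (1.960 + 0.842)² × 0.4375 / 0.0625 = 54.9. DE = 1 + (1.036 × 3 − 1) × 0.1 = 1.211. Then 54.9 × 1.211 / 0.9 = 73.9 per arm, or 24.6 villages, rounded up to 25. Power at 25 × 3: n_eff = 67.5 / 1.211 = 55.7, giving 78.6% (pooled) to 80.6% (unpooled). The 80% claim reproduces, but only with 25 villages per arm.

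**2. Ninety villages.**

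| Design, per arm | Children (total) | DE | n_eff | Pairwise power |
|---|---|---|---|---|
| 25 villages × 3 (as in 8.3) | 75 (375) | 1.211 | 55.7 | 79–81% |
| 18 villages × 4.17 | 75 (375) | 1.332 | 50.7 | 75–77% |
| 18 villages × 3 | 54 (270) | 1.211 | 40.1 | 64–67% |

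Row 2: DE = 1 + (1.036 × 4.17 − 1) × 0.1 = 1.332; n_eff = 67.5 / 1.332 = 50.7. Row 3: n_eff = 54 × 0.9 / 1.211 = 40.1.

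**3. The 90% in section 4.2.** With z_power = 1.282, n₀ = 73.6, and 73.6 × 1.211 / 0.9 = 99.0 per arm at 3 per village (about 104 with the pooled formula), against the 75 planned. With 75 per arm, ignoring clustering but keeping the 10% loss gives 86–87%. Ignoring both gives 89–91%. Only the last matches the summary, which itself says that 10% loss is allowed for.

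**4. Main effects, two arms against two.** Doubling n_eff under the same assumptions gives:
- 90 villages, 375 children: 2 × 50.7 = 101.4, power 96–97%
- 90 villages, 270 children: 2 × 40.1 = 80.3, power 91–92%

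**5. Section 11.7.1.** Five per cluster gives DE = 1 + 4 × 0.1 = 1.4, and 54.9 × 1.4 / 0.8 = 96 per arm, close to the stated 95. The calculation is coherent in itself, but its total is 4 × 95 = 380, for four arms.

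**The case against.** Four arguments carry weight.

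**Main effects come first.** Section 8.3 says that only the main effects of delivery mode and reminders are of primary interest, and words the effect for groups of arms. Those contrasts have 91–97% power even with 90 villages. This stands, and it limits the consequence: a reader might infer that the trial is underpowered for its main questions, and the documents do not support that. It does not rescue the stated figures. Section 8.3 also specifies each arm against Arm 1, and its 75 per arm with 80% power reproduces as one arm against one. Nor does it explain the summary's 90%, since the main-effect figure at 375 children is 96–97%.

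**The loss is small.** If 375 children are reached, pairwise power falls by about 4 points, while the choice of variance formula alone moves the protocol's own design by 2. This too stands. The larger error is 90% against 80%, which does not depend on the village count.

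**Bigger clusters are feasible.** Recruitment runs 30 months (section 8.10) at 2 to 4 children per village per year, or about 7.5 per village (3 × 2.5 years). So 375 from 90 villages is plausible and 64–67% is not inevitable. Holding 80% pairwise in 90 villages, however, needs about 4.8 to 5.1 children per village, or 432 to 459 in total, and the target remains 375.

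**The 102 villages.** Section 11.7.1 states "Each village cluster contributes 2 to 4 children/y with severe anaemia and there are 102 clusters in the catchment area". A reader might infer that 125 villages are therefore impossible. That figure sits in the text that still describes a four-arm trial, so it is weak evidence. The contradiction rests on the 90.

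**Conclusion.** The protocol contradicts itself on the number of villages (125 against 90), the power for 75 children per arm (80% against 90%) and the design being sized (five arms and 375 against four arms and 380).

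If 90 villages is right, pairwise power against Arm 1 is about 75–77% provided 375 children are recruited, and about 64–67% at 3 per village. The 90% in section 4.2 is not met pairwise with either village count; even 125 villages give 79–81%.

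These figures assume a two-sided test, the protocol's ICC, loss and cluster-size variation, and no multiplicity adjustment. They ignore any gain or loss from matching. The documents do not settle which village count governs, and they do not show that the main-effect comparisons lack power.

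**What to change.** First settle the number of villages and use it throughout sections 4.2, 8.2, 8.3 and 8.7.4.2.

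If it is 90:
- Restate 8.3 with 18 villages per arm, about 4.2 children per village, a design effect of about 1.33 and pairwise power of about 75–77%, conditional on reaching 375 children. State the sidedness of alpha.
- Give the power of the two-arm-versus-two-arm main effects separately: about 96–97% at 375 children and 91–92% at 270.
- If the sponsor wants 80% pairwise in 90 villages, raise the target to about 430–460 instead.

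If it is 125, the 80% in 8.3 can stay, and the site and randomisation sections must change.

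In either case, replace the 90% in section 4.2 with the matching figure and name the contrast it belongs to. Delete the four-arm, N=380, 20%-loss calculation from 11.7.1.

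The cost is protocol wording and a slightly less favourable stated pairwise power. Restating the figures needs no extra children or villages; raising the target would need about 55 to 85 more children.

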##### 8.7.4.2 Randomisation procedure at discharge

The unit of randomization will be the villages, defined as the smallest administrative unit overseen by a Village headman. A group Village headman oversees several villages. Ninety (90) villages in the catchment areas of Zomba district located in the southern region of Malawi will be involved in the study. Zomba Central Hospital participated in previous related studies [1, 15-17] and is particularly suitable for the delivery trial because of the existing linkages with community based health care providers and rural clinics within their catchment areas. A 1:1 allocation ratio will be used. To minimize imbalances across groups with respect to baseline malaria prevalence and risk factors for malaria, location-specific baseline information on malaria indicators, such as the prevalence of positive RDTs or microscopy in the 12-month period prior to the trial (Under-five registry data) will be considered in selection of villages.

Randomisation will be done by opening a single concealed envelope, which will contain the cluster and study arm.

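### Section 8.3 computes its 80% power for 125 villages, but the trial is fixed at 90; at N=375 the single-arm comparisons with Arm 1 have about 75–77% power

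*Protocol*

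**What the plan says.** Section 8.3 sets out the calculation as "a sample size of 25 clusters of an average of 3 children per village (75 children per arm, N=375 overall (for 125 clusters" across the five arms. It claims 80% power for 50% against 75% uptake, with ICC 0.1, 10% loss to follow-up, a squared coefficient of variation of cluster size of 0.036 and alpha 0.05. The comparison it describes is pairwise: "each of the four intervention arms will be compared to the control arm". The same section also says that the main effects of delivery mode and of reminders are what is of primary interest.

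The number of villages is stated elsewhere. Section 8.2 gives the site as "90 villages in the catchment areas of Zomba Central hospital in southern Malawi", and the section 4.2 summary gives the same number. Section 8.7.4.2 says "Ninety (90) villages in the catchment areas of Zomba district located in the southern region of Malawi will be involved in the study", makes the village the unit of randomisation, and adds "A 1:1 allocation ratio will be used".

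Two further places bear on the point. The section 4.2 summary attaches 90% power to the same 75 children per arm. Section 11.7.1 carries a different calculation (2x2 factorial, four arms, 19 clusters of 5 per arm, N=380, 20% allowance for loss or unequal cluster sizes) and says that "there are 102 clusters in the catchment area".

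**The concern.** In a cluster-randomised trial the number of clusters largely determines power. Section 8.3 takes its power from 25 villages per arm, while three other places fix a total that allows only 18. Nothing in the protocol reconciles 125 with 90. If 375 children come from fewer villages, each village contributes more of them, the design effect grows and the effective sample size shrinks. The stated 80% then belongs to a design other than the one to be run. The village count also fixes the allocation list, the matched sets and the degrees of freedom, so it needs a single value.

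**Working it through.** **Inputs from section 8.3.** 50% vs 75%; ICC 0.1; CV² 0.036; 10% loss; 75 children per arm (N=375). Villages: 125 in section 8.3; 90 in sections 4.2, 8.2 and 8.7.4.2.

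**Assumptions.** Two-sided alpha 0.05, since sidedness is not stated. Equal allocation of villages, so 90/5 = 18 per arm. CV² is kept at 0.036 when the mean cluster size changes.

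**Formulas.** With k villages per arm and m children per village:
- Design effect DE = 1 + ((1 + CV²)·m − 1)·ICC.
- Effective n per arm = k·m·0.9 / DE.
- SE1 = √((0.25 + 0.1875)/n); SE0 = √(2 × 0.625 × 0.375/n).
- Power, pooled variance under the null = Φ((0.25 − 1.96·SE0)/SE1).
- Power, unpooled = Φ(0.25/SE1 − 1.96).

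Each range below runs from pooled to unpooled.

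**Step 1: reproduce the stated figure (25 villages x 3).**
- DE = 1 + (1.036 × 3 − 1) × 0.1 = 1.211.
- n = 67.5/1.211 = 55.7; SE1 = 0.0886; SE0 = 0.0917.
- Pooled: Φ((0.25 − 0.1798)/0.0886) = Φ(0.79) = 78.6%.
- Unpooled: Φ(2.82 − 1.96) = 80.6%.

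The stated 80% is recovered, so 25 villages per arm is the real basis of the claim.

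**Step 2: 90 villages, N=375 kept (18 villages x 75/18 = 4.17).**
- DE = 1 + (1.036 × 4.17 − 1) × 0.1 = 1.332.
- n = 67.5/1.332 = 50.7; SE1 = 0.0929; SE0 = 0.0962.
- Pooled: Φ((0.25 − 0.1885)/0.0929) = Φ(0.66) = 74.6%.
- Unpooled: Φ(2.69 − 1.96) = 76.8%.
- A t reference on 2 × (18 − 1) = 34 df gives 74.4%.

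The loss from step 1 is 4.0 points pooled (78.6 − 74.6) and 3.8 points unpooled (80.6 − 76.8).

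**Step 3: can 375 be reached from 90 villages?** Section 8.3 gives 3 children per village per year, and section 8.10 gives 30 months of recruitment. 90 × 3 × 2.5 = 675 children, or 90 × 2 × 2.5 = 450 at the low end of 2 per year. At the mean rate, 375/270 = 1.39 years, about 17 months before refusals. The target is feasible.

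**Step 4: pooled main effects with 90 villages, N=375, the same 25-point difference.**
- SMS vs no SMS (Arms 2 and 5 vs Arms 1 and 4, 36 vs 36 villages): effective n = 36 × 4.17 × 0.9/1.332 = 101.4 per side, power about 96%.
- Delivery mode (54 vs 36 villages): effective n = 152.1 vs 101.4, power about 98%.

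**Step 5: hypothetical stop at 3 children per village (18 x 3, N=270).** DE 1.211, n = 48.6/1.211 = 40.1, power 64.3–66.8%.

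**Step 6: what would keep the 80% figure.** At N=375 with 18 villages per arm, 50% vs 76% has 78.2% (pooled) to 80.4% (unpooled), and 50% vs 77% has about 82–84%. Keeping 50% vs 75% at 80% would need about 4.7 (unpooled) to 5.1 (pooled) children per village, roughly 425–460 in total.

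**The case against.** The strongest reply is that little is lost. At the planned N the drop is about 4 points, and section 8.3 says main effects are the primary interest; on the same inputs these remain at 96% or more. Both parts stand and set the size of the point. They do not remove it, because section 8.3 also says that each arm is compared with Arm 1 and computes its power from the 75 children of a single arm. The 80% is therefore a pairwise figure, and at 90 villages it is not met.

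Two stronger readings are tempting. A reader might infer that enrolment will end at 270 children with power near 65%, because section 8.3 uses 3 children per village. The documents do not support this: 3 is a yearly rate, recruitment lasts 30 months, no village is capped, and 375 is given as the target in sections 4.1, 4.2 and 8.3.

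A reader might also infer that 125 villages are impossible because section 11.7.1 counts 102 clusters in the catchment. That section still describes a four-arm trial that differs from the current plan in arms, clusters per arm, N and loss allowance, so its village count may be out of date too. It is supporting evidence only; the contradiction between 125 and 90 does not depend on it.

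**Conclusion.** The point holds as a mismatch with a modest, quantified effect. The 80% in section 8.3 belongs to 125 villages, and the trial is fixed at 90. With 375 children, power for one arm against Arm 1 is about 75–77%, against 79–81% for the design as calculated. This rests on 18 villages per arm, a two-sided 0.05 level, an unchanged CV² of 0.036, and the plan's own ICC and uptake rates. It does not show that the trial is badly underpowered overall, since the pooled main effects are well covered if they too differ by 25 points. It should be corrected because a stated power is wrong for the design to be run, and correcting it is cheap.

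**What to change.** Rewrite section 8.3 for 90 villages: 18 per arm, a mean of about 4.2 children per village, and enrolment to 375 in total with no stop at 3 per village. Delete the 25 and 125 cluster counts. State pairwise power of about 75–77% for 50% vs 75%, or about 80% for a difference of 50% vs 76–77%. Name one formula and use it for every figure, because 80% at 76% holds only with the unpooled normal formula. State the assumed variation in cluster size at the new mean.

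Changing section 8.3 alone is not enough. The 90% power in the section 4.2 summary would need about 104 children per arm even with clusters of 3 (77 × 1.211/0.9 = 103.6), so it must be corrected as well. The four-arm calculation and village count in section 11.7.1 should be replaced by the revised text.

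The cost is protocol wording and a slightly less favourable stated power. No extra children or villages are needed.
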